#### **4.3.5.Video**

All the simulation sessions will be videotaped, so as to be viewed for analysis of actions and interventions performed during the simulation scenario (evaluation of the global competence and strategies used to manage the induced stress). Furthermore, videos will also further be viewed for analysis by two other independent observers, who will not know the team members. The mean between the two supervisor scores will be used as the reference value. Interobserver reproducibility of the teamwork scale (leadership and communication) will be calculated. Stress

University Hospital of Poitiers - CHU de Poitiers Sim-Stress management strategies implemented by the senior physician will also re-evaluated. A comparison will be performed with the supervisors observing the live simulation sessions.

#### 4.3.6. Debriefing

All the simulation sessions will be followed by a debriefing session, according to Rudolph's method of "*good judgment*" (Rudolph 2006, Rudolph 2008), and led by supervisors previously trained in this technique (University course Training at the University of Paris Descartes).

#### 4.3.7. Simulation session repetition

The frequency of repeated simulation sessions will be one of the varying parameters, and will define distribution into one of two randomized groups, necessary for providing answers to secondary objectives. Repetition will take place either every 6 weeks i.e. 9 / year (group 1), or every 6 months i.e. 3 / year (group 2).

### 4.4. Study schedule

#### 4.4.1. Time schedule of measurements

Time schedule of measurements

| Variables         |                    | day prior | Before Sim | Sim | Post Sim | Debrief | Post debrief | H+2 | 1 week | 1 month |
|-------------------|--------------------|-----------|------------|-----|----------|---------|--------------|-----|--------|---------|
| PERFORMANCE       | Global Performance |           |            | X   |          |         |              |     |        |         |
|                   | IO access          |           |            | X   |          |         |              |     |        |         |
|                   | Leadership (BAT)   |           |            | X   |          |         |              |     |        |         |
|                   | Teamwork (CTS)     |           |            | X   |          |         |              |     |        |         |
| STRESS PARAMETERS | Salivary cortisol  | X         | X          |     | X        |         | X            |     |        |         |
|                   | Holter parameters  | X         | X          | X   | X        | X       | X            | X   |        |         |
|                   | BP HR              | X         | X          |     | X        |         | X            |     |        |         |
|                   | SOM                |           | X          | X   |          |         |              |     |        |         |
|                   | STAI scale         | X         | X          |     | X        |         | X            |     |        |         |
|                   | EIS-R scale        |           |            |     |          |         |              |     | X      |         |
|                   | PCLS scale         |           |            |     |          |         |              |     |        | X       |

This plan will be repeated on each and every simulation session, that either every 6 weeks (as concerns the teams of group 1) or every 6 months (as concerns the teams of group 2).

#### **4.4.2. Quantification of sessions and various evaluations**

##### 4.4.2.1. Number of participants included in the study

12 teams of 4 persons = **48 participants**

##### 4.4.2.2. Number of team simulation sessions:

Participants of group 1: 6 teams x 9 sessions = 54 simulation sessions

Participants of group 2: 6 teams x 3 sessions = 18 simulation sessions

TOTAL = 54 + 18 = 72 team stimulation sessions

##### 4.4.2.3. Number of individual simulation sessions :

Group 1: 6 teams x 4 members per team x 9 sessions = 216

Group 2: 6 teams x 4 members per team x 3 sessions = 72

TOTAL = 216 + 72 = 288 individual simulation sessions

##### 4.4.2.4. Number of Holter recordings

Group 1: 9 Holter recordings by participant

Group 2: 3 Holter recordings by participant

Total: 1 Holter recording per session and per participant, that is, **288 Holter recordings**

##### 4.4.2.5. Number of Heart Rate and Blood Pressure measurements

Measurements will be obtained the day before the session, then just before and just after simulation, as well as after debriefing that is 4 times per simulation session.

Group 1: 36 measurements per participant

Group 2: 12 measurements per participant

Total: 288 x 4 = 1152 blood pressure and heart rate measurements

##### 4.4.2.6. Number of salivary cortisol concentration measurements

Salivary cortisol concentrations will be measured the day before the session, then just before and just after simulation, as well as after debriefing that is 4 times per simulation session.

Group 1: 36 cortisol concentration measurements per participant

Group 2: 12 cortisol concentration measurements per participant

Total: 288 x 4 = 1152 cortisol concentration measurements

#### **4.5. Description of measures taken to reduce or avoid bias**

##### **4.5.1. Drawing lots**

##### 4.5.1.1. Drawing lots will constitute representative samples

Lists of persons corresponding to each of the 4 professional statuses previously defined, will be established, and will serve as the basis of random drawing lots, for allocation into each of the categories, with samples representative of each professional status, thus avoiding any selection bias. The sample size (24 persons per group) will be the double of that required by the protocol, so as take into account possible participation refusals. Those selected by the drawing lots will be contacted in the order of appearance on the drawing lots list, until 12 consenting participants per group are obtained.

Teams consisting 4 participants, one from each representative status, will be established by following the order of appearance on drawing lots list. As an example, Team 1 will consist of the 1st person on the drawing lot list who will have given consent, and who will abide by all the inclusion / exclusion criteria pertaining to each of the 4 professional statuses. It is thus that 12 teams will be constituted.

##### 4.5.1.2. Drawing lots for random distribution of each team into one of the 2 of simulation session programs

Once the teams have been constituted, drawing lots will be performed according to a list that will be previously established by the study's methodologist, so as to distribute the 12 teams in 2 groups of 6 teams :

**Group 1** will be constituted by 6 teams of 4 persons each, and each of these teams will undergo simulation sessions once every **6 weeks**, for a total of 9 sessions in 12 months.

**Group 2** will be constituted by 6 teams of 4 persons each, and each of these teams will undergo simulation sessions once every **6 months**, for a total of 3 sessions in 12 months.

##### **4.5.2. Homogeneity of the study's population**

We have established relatively narrow inclusion criteria, so as to homogenize participants' training and/or professional experience for each of the four statuses.

#### **4.5.3.Methods of assessment using objective evaluation scales**

All the assessments using objective evaluation will be made by two observers, independent of each other, and in single manner, as far as their affectation to both groups and management of scenarios is concerned. Calculation of intra-class correlation coefficients will be performed for each of the scales used evaluation, even if such scales may have already been validated, so as to measure inter-observer reproducibility.

#### **4.6. Study duration**

Total duration of the study is estimated at **24 months**

Total duration of participation in the study for each participant: **12 months**

Starting from very first inclusion, the sponsor must immediately, and without any delay, inform the proper authorities and France's Protection Committee of Human Subjects (CPP - "Comité de Protection des Personnes) as to the effective date of study onset (effective date of study onset = date of signature of consent made by the first participant included in the study).

The date of study end will be transmitted by the sponsor to the France's National Agency of Medication and Health Product Security ("ANSM - Agence Nationale de Sécurité du Médicament et des produits de santé") and to the CPP within a period of 90 days following that date.

The date of study end corresponds to the participation end term of the last participant included in the study, or if need be, **to the end term as defined in the protocol.**

#### **4.7. Description of rules concerning either definitive or temporary withdrawal**

##### **4.7.1.Participant withdrawal from this study**

Participants will be allowed to withdraw their assent and ask leave the study at any moment, and for whatever reason. In case of a premature exit, the investigator must inform as to the reasons in as complete a way as possible. The investigator will be able to interrupt, either temporarily or definitively, the participation of a participant in the study, for any reason that may be considered as being in the best of interest to the participant, especially in the case of serious adverse effects.

##### **4.7.2.Partial or complete study interruption**

This study may eventually be interrupted prematurely, in the case of unexpected and severe adverse events, that would merit an in depth review as to the strategy's profile. Similarly, unforeseen events that would not allow the study objectives to be credibly attained can incite the sponsor to interrupt the study prematurely.

The University Hospital of Poitiers (CHU de Poitiers) reserves the right to interrupt this study, at any time, should the objectives of inclusion not be attained. In case of a premature interruption of this study, this information will be transmitted by the sponsor to France's Protection Committee of Human Subjects (CPP - "Comité de Protection des Personnes) within the next 15 days.

#### **4.8. Identification of all data to be collected directly in observation manuals and to be considered as data sources**

A CRF paper will be provided to the investigators, in which clinical data will be directly noted by the included participants.

Data collected in the CRF will so be able to be considered as data sources. The investigator should date and sign this copy at the end of data collection.

### **5. INCLUSION AND EXCLUSION CRITERIA**

#### **5.1. Inclusion criteria**

- All participants in the trial study will be volunteers;
- Age  $\geq 18$ ;
- All participants will be legally free and not subject to any custody, guardianship, or tutelage;
- Participants should all adhere to France's Social Security Health regime;

University Hospital of Poitiers - CHU de Poitiers Sim-Stress

- Free, prior, clearly informed and written consent
- Signed agreement allowing for video-recordings that will be strictly and exclusively used for evaluation purposes during this study;
- Four-member teams:
  - 1/- Emergency physician of the Poitou-Charentes region and its surroundings, having professional experience of less than seven years and having obtained a complementary University Course in Pediatric Emergency Procedures (Diplôme Universitaire des Gestes d'Urgence en Pédiatrie) during the last 3 years, which abides by the latest recommendations of advanced paediatric resuscitation, established in 2010 by the AHA - *AMERICAN HEART ASSOCIATION* (Kleinman, 2010) and the ERC - *EUROPEAN RESUSCITATION COUNCIL* (Barient,2010);
  - 2/ Medical Resident ("interne") currently registered in a Complementary Specialized Diploma of Emergency Medicine ("DESC - *Diplôme d'Études Spécialisées Complémentaires* - de Médecine d'Urgence") at the University of Poitiers, and having received training in pediatric emergency procedures.
  - 3/ Registered Nurse of the Emergency Medical Service and Emergency Medical and Resuscitation Mobile Services ("SAMU - *Service d'Aide Médicale d'Urgence*" SMUR - " *Service Mobile d'Urgence et de Réanimation*") of the University Hospital of Poitiers (CHU de Poitiers), having a professional experience of less than seven years, and having obtained a EPILS - *European Pediatric Immediate Life Support* - diploma during the last two years;
  - 4/-Ambulance driver of the of the Emergency Medical Service and Emergency Medical and Resuscitation Mobile Services ("SAMU - *Service d'Aide Médicale d'Urgence*" SMUR - " *Service Mobile d'Urgence et de Réanimation*") of the University Hospital of Poitiers (CHU de Poitiers), having a professional experience of less than seven years.

## **5.2. Non-inclusion Criteria**

- Age < 18 years
- Current participation in another clinical research study, with an exclusion period of at least month between the two research protocols;
- Participants not benefiting from a Social Security Health Regime ("Sécurité Sociale");
- Pregnant or breast-feeding women, women at an age to procreate and not using an effective contraception method (either hormonal / mechanical [*per os*, injectable, transcutaneous, implantable, intra-uterine device] or surgical [tubal ligation, hysterectomy, total ovariectomy];
- Medical and/or psychiatric antecedents that could influence the state of stress.
- Cardiac or convulsive neurological antecedents.
- Pacemaker or automatic internal cardioverter-defibrillator bearers;
- Participants using cardiotropic agents and/or beta-2 mimetic bronchodilator medication (possible modification of cardiac electrophysiological parameters).

## **5.3. Per-Study Exclusion Criteria (Subject Withdrawals or Discontinuation)**

- Disregard of evaluation dates and schedules that could thus either compromise the simulation sessions or influence the parameters being evaluated.
- Exclusion of the entire team in case of withdrawal of one of its members.

## **5.4. Recruitment modalities**

According to the participants' status, the mode of recruitment will differ as follows:

- 12 senior emergency physicians of the Poitou-Charentes region and its surroundings, having professional experience of less than seven years and having obtained a complementary University Course in Pediatric Emergency Procedures (Diplôme Universitaire des Gestes d'Urgence en Pédiatrie) during the last 3 years, which abides by the latest recommendations of advanced paediatric resuscitation, established in 2010 by the AHA - *AMERICAN HEART ASSOCIATION* (Kleinman, 2010) and the ERC - *EUROPEAN RESUSCITATION COUNCIL* (Barient,2010);
- 12 Medical Residents ("internes") currently registered in a Complementary Specialized Diploma of Emergency Medicine ("DESC - *Diplôme d'Études Spécialisées Complémentaires* - de Médecine d'Urgence") at the University of Poitiers, and having received training in pediatric emergency procedures.
- 12 Registered Nurses of the Emergency Medical Service and Emergency Medical and Resuscitation Mobile Services ("SAMU - *Service d'Aide Médicale d'Urgence*" SMUR - " *Service Mobile d'Urgence et de Réanimation*") of

University Hospital of Poitiers - CHU de Poitiers Sim-Stress

the University Hospital of Poitiers (CHU de Poitiers), having a professional experience of less than seven years, and having obtained a EPILS - European Pediatric Immediate Life Support - diploma during the last two years;

- 12 Ambulance drivers of the of the Emergency Medical Service and Emergency Medical and Resuscitation Mobile Services ("SAMU - Service d'Aide Médicale d'Urgence" SMUR - " Service Mobile d'Urgence et de Réanimation") of the University Hospital of Poitiers (CHU de Poitiers), having a professional experience of less than seven years.

For each of these statuses, an exhaustive list will be established serving as a basis for random sampling. The drawn lots of participants will be contacted by e-mail, to presentation them the study and to invite them to participate. Definitive, signed consent will be obtained the day before the first simulation session, in the presence of the coordinating investigator of this study.

The modalities of the drawing lots have been described in paragraph 4.5 .1

## **5.5. Procedure for exclusion from the study**

### **5.5.1.Participant study exclusion criteria and modalities**

#### **5.5.1.1. Subjects having recalled their assent and having asked withdraw from the study, will be excluded.**

The investigator will be able to interrupt the participation of a study participant for any reason that would be to the best of the subject's interests, and, in particular, in the case of serious adverse effects.

A participant will be excluded from the study in case of disregard of evaluation dates and schedules, that could compromise the simulation sessions or influence studied parameters.

The exclusion of any one member will result in the exclusion of the member's entire team, and will necessitate the integral inclusion of a new team.

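### Excluding and replacing a whole randomised team when one member leaves, with no allocation rule for the new team, can bias the secondary 9 versus 3 session comparison

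*Protocol*

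**What the plan says.** - **Unit and timing of randomisation.** Protocol Section 4.5.1.2 allocates teams, six to each group: "Once the teams have been constituted, drawing lots will be performed according to a list that will be previously established by the study's methodologist".
- **Team exclusion.** Section 5.3 lists "Exclusion of the entire team in case of withdrawal of one of its members". Section 5.5.1.1 widens this to any exclusion: "The exclusion of any one member will result in the exclusion of the member's entire team". The same sentence requires that a complete new team be enrolled.
- **Triggers.** One is withdrawal. Section 4.7.1 says: "Participants will be allowed to withdraw their assent and ask leave the study at any moment, and for whatever reason". The other is failure to keep the schedule. Section 5.5.1.1 says: "A participant will be excluded from the study in case of disregard of evaluation dates and schedules", limited there and in Section 5.3 to breaches that could compromise the sessions or influence the measured parameters.
- **Data of those who leave.** Section 5.5.2 allows analysis of data from participants who withdrew consent, if they agree. It does not mention their teammates, or teams removed over dates.
- **Analyses affected.** Section 9.1.4 compares the relative change from T0 to the end of the programme between groups by a t-test. Section 9.1.5 compares the stress markers between groups. Section 9.1.3 mentions mixed models over all sessions only as something envisaged. Section 9.5 asks that missing data be recorded and explained.

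No section says which group a new team joins, whether it is randomised, or whether an excluded team is still analysed in its allocated group.

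**The concern.** Teams are randomised once formed and members may leave at any time in the following 12 months, so the rule acts after allocation. It takes a randomised unit out and puts another in by an unstated route. The 9 versus 3 session comparison is the trial's only randomised comparison. If the teams that reach the end differ from those that were randomised, and differ more in one arm, the comparison no longer rests on randomisation alone. The programme itself could produce such a difference: a Group 1 team has three times as many sessions to keep, each with the full measurement plan of Section 4.4.1, and failure to keep the schedule is a mandatory trigger. With six teams per arm, each lost team is a sixth of the arm.

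**Working it through.** **1. The plan's own counts.** Section 4.4.2.3 gives "Group 1: 6 teams x 4 members per team x 9 sessions = 216" and, for Group 2, 6 x 4 x 3 = 72. Both reproduce. Per team this is 216/6 = 36 member-sessions in Group 1 and 72/6 = 12 in Group 2.

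**2. Exclusion if risk follows sessions.** The protocol states no exclusion rate, so let p be an assumed probability, per member-session, of an event that removes the team, equal in both arms and independent between sessions. Then P(team excluded) = 1 - (1 - p)^36 in Group 1 and 1 - (1 - p)^12 in Group 2. The expected number lost among the six original teams is 6 times that.

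| Assumed p | Group 1 | Group 2 | Expected teams lost of 6 | Ratio |
|---|---|---|---|---|
| 0.5% | 16.5% | 5.8% | 0.99 vs 0.35 | 2.8 |
| 1% | 30.4% | 11.4% | 1.82 vs 0.68 | 2.7 |
| 2% | 51.7% | 21.5% | 3.10 vs 1.29 | 2.4 |
| 5% | 84.2% | 46.0% | 5.05 vs 2.76 | 1.8 |

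**3. Exclusion if risk follows calendar time only.** Let q be an assumed 12-month withdrawal probability per person, the same in both arms. Then P(team excluded) = 1 - (1 - q)^4.

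- q = 5%: 1 - 0.95^4 = 18.5% of teams in each arm, or 2.2 of 12.
- q = 10%: 1 - 0.90^4 = 34.4% of teams in each arm, or 4.1 of 12.

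The ratio between arms is 1.0. Across the two mechanisms and the values shown, it therefore lies between 1.0 and about 2.8.

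**4. From exclusion to bias.** Suppose there is no true effect and the team outcome y is standard normal in both arms. Let the log-odds of exclusion per member-session be logit(p) - ln(OR) x y, so that a team 1 SD worse has OR times the odds. A team completes with probability (1 - p_y)^36 or (1 - p_y)^12, where p_y is its own per-session risk. The bias is the difference between arms in the mean of y among completing teams.

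| Assumed p | OR = 1 | OR = 1.5 | OR = 2 |
|---|---|---|---|
| 0.5% | 0 | 0.05 SD | 0.09 SD |
| 1% | 0 | 0.10 SD | 0.16 SD |
| 2% | 0 | 0.18 SD | 0.26 SD |

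At p = 1% and OR = 2, for example, completing teams average 0.255 SD in Group 1 and 0.097 SD in Group 2, a spurious difference of 0.158 SD in favour of Group 1. With OR = 1 there is no bias, however many teams are lost.

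**5. Scale.** With the team as the unit, the normal approximation gives a difference detectable with 80% power, six against six, of (1.96 + 0.84) x sqrt(2/6) = 1.62 SD. The spurious differences above are well below that. They shift the estimate but would not by themselves usually decide a test.

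**The case against.** The rule has an operational reason. Performance is scored on a fixed team of four roles, and a session run with three people does not yield a comparable team score. Stopping an incomplete team's sessions is therefore defensible, and that part of the objection stands. It does not justify removing the team from the comparison.

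Five stronger readings are tempting, and the documents do not support them.

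- *Group 1 will lose more teams.* This needs a risk tied to sessions. A job move or pregnancy follows the calendar and affects both arms alike, only consequential schedule breaches count as a trigger, and one person's attendances are correlated, which weakens the independence used in step 2. A higher rate in Group 1 is plausible, but its size is unknown.
- *The new team fills the vacated arm.* The protocol is silent. Full inclusion of a new team could mean repeating the draw of Section 4.5.1.2. What can be said is that its allocation is undefined.
- *The data of the three remaining members are thrown away.* Section 5.5.1.1 excludes people from the study and does not say that collected data are dropped. Analysis populations may also be set in a statistical analysis plan that is not shown. But the final-score t-test in Section 9.1.4 cannot use a team that stopped early, whatever population is defined.
- *One or two replacements would change the answer.* Steps 4 and 5 do not show this, and there is no bias if exclusion is unrelated to outcome. Missed dates may reflect duty rosters and nothing more.
- *A replacement cannot fit into the 24 months.* With one year of enrolment and one of participation, a new team that starts by about month 12 can finish. Only later exclusions cannot be made good within that plan.

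**Conclusion.** The point holds in a limited form. Sections 5.3 and 5.5.1.1 remove randomised teams after allocation and require new ones without an allocation rule, and no other section offsets this. It can bias the 9 versus 3 session comparisons in Sections 9.1.4 and 9.1.5, most clearly the T0-to-final t-test.

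The size rests on assumptions, because the protocol gives no rate. Loss differs by arm if risk follows member-sessions and is equal if it follows calendar time. Bias needs a link between exclusion and stress or performance: 0.05 to 0.26 SD over the assumed range of p from 0.5% to 2% with 1.5 to 2 times the odds per SD, and zero without such a link.

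A reader might infer that the trial's main result is at risk. The documents do not support that. The protocol labels this comparison secondary, and the stress-performance correlation that sets the sample size in Section 9.2 pools all participants and is not the target.

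**What to change.** Reword Sections 5.3 and 5.5.1.1, and align Section 9.1.4, as follows.

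1. A team may stop its sessions when it is no longer complete. No team scores are taken from an incomplete team.
2. Every randomised team stays in the analysis in its allocated group, with all team scores and individual data collected up to that point, subject to the consent rule in Section 5.5.2.
3. The group comparison uses a mixed model over sessions, of the kind Section 9.1.3 already envisages, so that a final score is not required. This reduces the bias. It removes it only if stopping can be explained by data already observed.
4. Any additional team receives its own random allocation from an extension of the methodologist's list, does not replace a randomised team, and is identified separately. Results are given with and without such teams.
5. Exclusions are reported by group, with the reason and the session at which they occurred.

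The cost is protocol wording, a longer allocation list and the use of data already collected. The downside is that some team series will be incomplete.
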